### Participants

The target population are 5000 young adults from the general population. Inclusion criteria are an age between 18 and 21 at baseline and the provision of an informed consent. Exclusion criteria are insufficient mastery of the German language, a cognitive or physical inability to take part in the online questionnaire reported by a relative, for example reported by a relative, or the inability to follow the studies procedures, e.g., due to not having internet access.

Addresses of 15,000 young adults are provided by the Swiss Federal Office of Statistics. Participants are drawn at random from all individuals living in a private household in German-Speaking municipalities that did not already participate recently in another survey. We will send an invitation letter with the study information to all young adults by postal mail. The invitation letter also lists psychosocial services and helplines and a small giveaway in form of summer flower seeds. Participants have also the chance to take part in a participation-associated lottery with monetary winnings. For the first wave, participants can win 200 vouchers for a Swiss Supermarket chain for 50 CHF (approximately 55 US Dollars). For each of the next waves, they can win 75 vouchers for 50 CHF. Such incentives have been shown to increase response rates [45, 46]. The invitation letter contains an identification number and a link to the study webpage. Using their unique 6-digit identification number, participants can give their written informed consent electronically on REDCap [47, 48] by signing with their mouse or touch screen before starting to fill out the online questionnaires.

We expect a response rate of 30%. If the targeted sample size will not be reached, a second sample will be recruited via educational facilities such as universities, teacher training colleges or military training schools. A link to the study website with the full study information and the informed consent will either be posted on university webpages and other billboards or forwarded via intermediary student organisations. Invitations for follow-ups will be sent to the e-mail address provided by participants in the baseline questionnaire. For the follow-ups, two reminders per e-mail are planned for participants not replying to the invitation.

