Logistic regression analyses will be used to analyse predictors of service use and enrolment to the FACE intervention (as binary variables). Predictor variables are simultaneously entered in the model and include ACE, age, gender, socio-economic status and psychosocial functioning.

Where an influence of the COVID-19 pandemic is to be expected, we will adjust for the impact of the crisis on individuals to ensure that trends are not created by the consequences of the COVID-19 epidemic or conduct sensitivity analysis to gauge the effect of the COVID-19 crisis. For example, there may be a general improvement of mental health in case the pandemic is ending between two waves of our study, and it will be important to account for that when considering trends across the four waves.

*Justification of sample size:* The sample size of the epidemiological study is determined with consideration of the number of participants needed in the FACE intervention study, i.e., 350 participants. This sample size allows the detection of small effect sizes for the interaction between time (pre, post, follow-up) and the two treatment condition SSIP vs SER, mediation analyses with parallel mediators in a structural equation modelling framework and, a multi-group model for each treatment arm, and an accurate estimates of the regression coefficients, the variance components and the standard errors for multilevel analyses of the EMA data [75, 76], details will be reported elsewhere]. For the FACE *epidemiological study*, the sample size of 5000 at baseline is based on the expectations that 25% (n = 1250) of the participants report ACE and that a third of them (n = 375) give an informed consent for the intervention study and start the FACE self-help programme.

*Handling of missing data:* An attrition of 40% is expected in the fourth wave of the epidemiological study, resulting in a sample of about 3000 participants at the fourth wave. We will conduct missingness analyses which identify patterns and predictors of missingness and determine whether missing data are completely at random, at random or non-ignorable. If missingness at random is supported, we will use Multiple Imputations in Mplus [77]. Sensitivity analyses will compare the results of different ways of imputing missing data including complete case analyses and if appropriate full information maximum likelihood.

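### The fraction and the count for intervention uptake disagree (a third of 1,250 is 417, not 375), and the address draw is expected to give 4,500 participants, not 5,000

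*Protocol article*

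**What the plan says.** The justification of sample size, under Statistical analysis in the protocol article, ties the epidemiological sample to "the number of participants needed in the FACE intervention study, i.e., 350 participants". From a baseline of 5,000 it expects 1,250 people with ACE, a share of 25%. The words that lead from this step to the next are "of the participants report ACE and that a third of them", and the count printed for that next step, the people who agree to join the intervention study and begin its programme, is 375. This is the only numerical justification given for the baseline size.

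The paragraph on missing data in the same section expects 40% attrition by the last wave, "resulting in a sample of about 3000 participants at the fourth wave".

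The Participants section describes where the sample comes from: "Addresses of 15,000 young adults are provided by the Swiss Federal Office of Statistics", drawn at random from private households in German-speaking municipalities. It adds: "We expect a response rate of 30" per cent. The next sentence provides for a second sample through universities, teacher training colleges or military training schools if the target is missed. The Abstract repeats that condition.

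**The concern.** There are two mismatches, and they bear on each other.

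First, the fraction and the count for intervention uptake cannot both be right. The article prints 1,250 and then 375 as a third of it.

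Second, the address draw and the response rate do not multiply to the stated baseline. The second sample is worded as something that may happen, although the plan's own response rate implies that it will be needed to reach 5,000. That sample would be reached through postings and student organisations and not by random draw from the register, so a reader should be told that it is expected and roughly how large it is.

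The link between the two is the intervention need of 350. Whether the register sample alone would meet it depends on which uptake rate is meant, and the article leaves that open.

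**Working it through.** **Inputs.** From the justification of sample size: baseline 5,000; 25% with ACE (1,250); uptake one third, printed as 375; need 350. From Participants: 15,000 addresses; 30% response. From handling of missing data: 40% attrition by wave 4, about 3,000 left.

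**Step 1: reproduce the printed chain.**
- With ACE: 5,000 × 0.25 = 1,250. This agrees with the article.
- Starters: 1,250 ÷ 3 = 416.7, so 417. The article prints 375.
- Gap: 416.7 − 375 = 41.7, which is 11.1% of 375. Rounding does not explain it, since 1,250 × 0.33 = 412.5.
- Rate implied by the printed count: 375 ÷ 1,250 = 30.0%.
- Wave 4: 5,000 × (1 − 0.40) = 3,000. This agrees with the article.

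**Step 2: expected yield of the address draw.**
- 15,000 × 0.30 = 4,500.
- Shortfall: 5,000 − 4,500 = 500, and 500 ÷ 5,000 = 10%.
- Response needed for 5,000 from the register alone: 5,000 ÷ 15,000 = 33.3%.
- Register only, with ACE: 4,500 × 0.25 = 1,125.
- Register only, wave 4: 4,500 × 0.60 = 2,700.

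**Step 3: starters under each combination (need: 350).**

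| Baseline | With ACE | Uptake one third | Uptake 30% |
|---|---|---|---|
| 5,000 | 1,250 | 417 (meets) | 375 (meets) |
| 4,500 | 1,125 | 375 (meets) | 337.5, about 338 (misses) |

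**Step 4: baseline needed for 350 starters.**
- At one third: 350 × 3 ÷ 0.25 = 4,200.
- At 30%: 350 ÷ (0.30 × 0.25) = 4,667.

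The expected register yield of 4,500 lies between these two values. The choice between a third and 30% therefore decides whether the register sample alone would serve the intervention study.

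**The case against.** The strongest reply is that nothing of substance fails at the stated target. A baseline of 5,000 gives 375 or 417 starters, both above 350, and the printed 375 is the more cautious of the two. A third may simply be loose wording for 30%. The gap of 500 is also provided for: the sentence after the response rate introduces the second recruitment route, so 5,000 can be read as the target over both routes and 30% as the yield of the postal route alone. On that reading the two sections do not contradict each other.

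Most of this stands, and it limits the point. It does not remove the mismatch between fraction and count. Nor does it change the fact that a route worded as conditional is, at the plan's own response rate, the expected one.

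Three stronger inferences are tempting, and the documents do not support them.

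- A reader might notice that 4,500 × 0.25 ÷ 3 is exactly 375 and conclude that 375 was worked out from a baseline of 4,500. It may have been, but 30% of 1,250 also gives exactly 375 with no change of baseline, and the article prints 1,250 directly before 375. The origin cannot be settled from the text.
- A reader might infer that neither 5,000 nor 3,000 is supported. But 3,000 is exactly 60% of 5,000, 5,000 covers the need at either uptake rate, and the second sample offers a way to reach it.
- A reader might infer that 4,200 is enough and that the second sample should be used only below that number. That figure holds only at one-third uptake and leaves no margin. At 30% uptake it gives 4,200 × 0.25 × 0.30 = 315 starters. The article also sets the size with consideration of the intervention need, and its Discussion relies on a large sample to identify ACE patterns. A lower floor would be a change of design.

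**Conclusion.** The point holds in a limited form. The uptake fraction and its count disagree by about 42 people. The address draw is expected to fall 500 (10%) short of the target, so the second sample is the expected case. The adequacy of 5,000 for the intervention study is not in doubt at the stated rates. What is in doubt is whether the register sample alone would suffice: 375 starters at one third, about 338 at 30%.

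This rests on three assumptions: that the 30% response means people who become baseline participants; that the 25% prevalence and the uptake rate apply equally to both recruitment routes; and that attrition is 40% whichever route is used. The 2,700 at wave 4 applies only if the second sample is not recruited. If recruitment does reach 5,000, the 3,000 stands.

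**What to change.** In the justification of sample size, state one uptake rate with its matching count from 5,000: either one third with 417, or 30% with 375.

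In Participants, state that 15,000 addresses at a 30% response are expected to give about 4,500, and that about 500 are expected to come from the second sample.

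If the second sample is not to be used, restate the baseline as 4,500, with 1,125 reporting ACE and about 2,700 at wave 4. Give the starters at the chosen uptake rate (375 at one third, about 338 at 30%) next to the 350 needed.

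The cost is a few sentences of wording and, for the register alone, slightly less favourable figures. No analysis changes.

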### Statistical analysis

Significance level will be two-sided α = 0.05. Due to the large sample size, effect sizes will be prioritised over the significance level for the interpretation of the results. Cohort data will be analysed with a range of observed and latent variable models using Mplus that include person- and variable-centred approaches. Distinct patterns of ACE will be identified using a Latent Class Analysis based on the subtype and frequency of childhood experiences, for example patterns combining subtypes of child maltreatment, household dysfunctions or bullying by peers. Psychosocial functioning as primary outcome will be analysed in a variable- and a person-centered approach. For the variable-centered approach, a composite measure of psychosocial functioning will be computed using Factor Analyses including bifactor models. For the person-centered analyses, a Latent Profile Analysis is used to identify psychosocial adaption patterns, for example an average group, a resilient group, a moderately vulnerable group, and a highly vulnerable group.

The main hypotheses for the associations between childhood experiences, emotion regulation, social information processing and psychosocial functioning will be analysed using structural equation models with subtypes, dimensions, or patterns of childhood experiences as predictor and moderator variables and psychosocial functioning as outcome variable. (Moderated) mediation hypotheses will be tested using structural equation modelling with the simultaneous inclusion of dimensions of emotion regulation and social information processing variables as mediators linking childhood experiences with psychosocial functioning.

The trajectories of psychosocial adaptation, emotion regulation strategies and social information processing will be investigated with Growth- and Growth-Mixture models. For the longitudinal trajectories of psychosocial functioning across emerging adulthood, we expect to find a chronically dysfunctional group, a recovering group and a resistant trajectory group over time using Latent Growth Mixture Models. The effect of the use of mental health care services after baseline will be analysed with a Latent Transition Analysis where service use will be entered as predictor and the transition between the subgroups as outcome variable.

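### Multiple imputation is the main missing-data method for every model, including the growth-mixture and latent-transition models; unless the imputation allows for latent classes, late-wave class means are biased

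*Protocol article*

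**What the plan says.** All quotations are from the Protocol article, Methods, Statistical analysis.

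- **Main method:** "If missingness at random is supported, we will use Multiple Imputations in Mplus".
- **Role of the alternatives:** "Sensitivity analyses will compare the results of different ways of imputing missing data including complete case analyses and if appropriate full information maximum likelihood". FIML is therefore a check, and a conditional one.
- **Expected loss:** "An attrition of 40% is expected in the fourth wave of the epidemiological study, resulting in a sample of about 3000 participants at the fourth" (quotation cut one word before the sentence ends).
- **Models that use class structure over time:** "we expect to find a chronically dysfunctional group, a recovering group and a resistant trajectory group over time using Latent Growth Mixture Models", and a "Latent Transition Analysis where service use will be entered as predictor and the transition between the subgroups as outcome variable".
- **Profile analysis of the primary outcome:** "a Latent Profile Analysis is used to identify psychosocial adaption patterns". The wave or waves it uses are not stated.

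The missing-data rule is written once for all analyses. No mixture model is exempted, and the imputation model is not described. In the limitations part of the Discussion, the authors expect participants who develop worse to respond less often at follow-up, and say that multiple imputation can deal with this.

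**The concern.** A growth-mixture model assumes that the sample contains groups with different trajectories. If the imputation model treats everyone as one population, a dropout's later scores are drawn from the pooled regression and not from the trajectory of that person's class. The mixture model then estimates class trajectories partly from those draws. The late waves suffer most: they hold the most imputed values, and they are where a chronic and a recovering group should separate.

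This bias does not need MAR to fail. It comes from a mismatch between the imputation model and the analysis model. FIML relies on the same MAR assumption, but lets the mixture model itself deal with the missing waves.

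The stake is substantive. Under Objectives, distinct adaptation trajectories belong to the primary objective, and the plan gives effect sizes priority over significance. Biased class means are thus biased in the quantity that will be interpreted.

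**Working it through.** **The plan's own figure.** Baseline sample: "the sample size of 5000 at baseline is based on the expectations that 25% (n = 1250) of the participants report ACE". With 40% attrition, 5000 × (1 − 0.40) = 3000, as the article states. So 5000 − 3000 = 2000 wave-4 records would be imputed.

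**Inputs from the document.** N = 5000; four waves; 60% retained at wave 4; three trajectory classes (chronic, recovering, resistant).

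**Inputs assumed (not in the document).**
- Class shares of 15%, 15% and 70%, and a within-class SD of 1.
- The chronic class stays 2, 3 or 4 SD below the resistant class. The recovering class starts level with the chronic class and reaches the resistant level at wave 4, so the true chronic-recovering gap at wave 4 is 2, 3 or 4.
- Monotone MAR dropout with equal yearly retention 0.60^(1/3) = 0.843, giving 5000, 4217, 3557 and 3000. Dropout is either unrelated to the last score or related to it (logit slope 0.5 per SD, worse scores leaving more).

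**Method.** A three-class normal mixture with free class means and common covariance was fitted (a) to the incomplete data by FIML and (b) to five imputations from a single-population normal model. There were six replicates per scenario, and the fit was started at the true values.

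**Formulas.** Gap = recovering mean − chronic mean at wave 4. Kept = estimated gap ÷ true gap. Lost = 1 − kept.

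| True gap | Dropout | FIML means (chronic, recovering) | FIML gap (kept) | MI means (chronic, recovering) | MI gap (kept; lost) |
|---|---|---|---|---|---|
| 2 | unrelated | −1.973, −0.005 | 1.968 (98%) | −1.783, −0.220 | 1.563 (78%; 22%) |
| 2 | worse leave more | −1.911, 0.068 | 1.979 (99%) | −1.536, −0.180 | 1.356 (68%; 32%) |
| 3 | unrelated | −2.989, −0.039 | 2.950 (98%) | −2.711, −0.339 | 2.372 (79%; 21%) |
| 3 | worse leave more | −2.944, −0.016 | 2.928 (98%) | −2.246, −0.418 | 1.828 (61%; 39%) |
| 4 | unrelated | −3.991, 0.002 | 3.993 (100%) | −3.622, −0.410 | 3.212 (80%; 20%) |
| 4 | worse leave more | −4.003, 0.046 | 4.049 (101%) | −2.861, −0.604 | 2.257 (56%; 44%) |

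**What did not move much.** Under MI, estimated class shares were within about 2 percentage points of the truth. Correct classification was 1 to 2 points lower than under FIML.

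**Other assumptions.**
- One separate simulation used 4,500 people, shares of 10%, 15% and 75%, and MAR dropout to 60% retention. The true gap was 0.10 + 1.80 = 1.90. FIML gave 0.08 + 1.81 = 1.89. Single-population MI gave −0.17 + 1.40 = 1.23, a loss of 1 − 1.23/1.90 = 35%.
- Another, with a true gap of about 1.9, gave about 1.55 under score-unrelated dropout (1 − 1.55/1.9 = 18%) and about 1.3 under score-related dropout (1 − 1.3/1.9 = 32%). Adding auxiliary variables or skewed errors did not remove the shrinkage.

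**The case against.** **The imputation model is not stated.** A reader might infer that the plan imputes from a single-population model. The article does not say so. Imputing from the mixture model would also be multiple imputation and would satisfy the wording. The model may be set out in an analysis plan that is not shown, and an article may leave it there. This stands, and it makes the bias conditional. What remains is the ranking, which is stated: multiple imputation first, FIML optional, one rule for all models.

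**The sensitivity analysis would reveal the problem.** In part. A comparison with FIML would show a divergence of this size, but it is planned only "if appropriate full information maximum likelihood", and a check does not settle which result is reported as the main one.

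**Not all latent-variable models are affected.** This stands. A profile analysis of baseline data would be little touched by attrition. The main hypotheses are tested with structural equation models, and nothing here shows that multiple imputation harms those or the factor models.

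**The classes themselves survive.** This stands too. A reader might infer that the groups would be lost or miscounted. Class shares hardly moved, and choosing the number of classes was not tested. Pooling of fit statistics and label switching across imputations are details an article can leave to the analysis plan, and are not counted here.

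**The simulations favour FIML.** They fit the correct three-class model, and the six-scenario run started at the true values. That limits the exact percentages, but the direction was the same in every scenario.

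**Conclusion.** The point holds in a conditional and narrow form. The plan ranks multiple imputation above FIML for every analysis and makes no exception for growth-mixture and latent-transition models. Unless the imputation allows for the classes, which the article does not state, late-wave class means are biased even when MAR holds exactly. At 40% wave-4 attrition the chronic-recovering gap shrinks by about 20-22% if dropout is unrelated to scores and by about 32-44% if worse scores drop out more. The second pattern is the kind of attrition the Discussion expects. Under the same MAR assumption, FIML stays within about 2%.

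These sizes rest on assumed class shares, separation and dropout strength. One further run put the loss under unrelated dropout slightly lower, at 18%. Latent-transition models were not simulated; they are included because they too estimate class structure from follow-up waves. The Discussion's statement that multiple imputation can deal with selective attrition does not hold for these models if the imputation ignores the classes. The documents do not support a general claim that the primary analyses are invalid, or that all latent-variable models need a different method.

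**What to change.** In the missing-data paragraph:

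- Make FIML under MAR, with auxiliary variables where feasible, the main method for the growth-mixture and latent-transition models, and for any profile analysis that uses follow-up waves.
- For those models, use imputation that allows for the latent classes as the sensitivity analysis.
- Keep multiple imputation for the logistic regressions, and leave the non-mixture structural equation and factor models as planned.
- State which wave or waves the profile analysis uses, so that it is clear which rule applies.

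In the Discussion, qualify the sentence on selective attrition: for mixture models, multiple imputation addresses it only if MAR holds and the imputation model reflects the classes.

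The cost is a change of wording, with the same software. The downsides are longer run times and the need to handle auxiliary variables explicitly in the mixture models.

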## Discussion

Adverse childhood experiences have a high prevalence, cause considerable personal suffering and are a well-established transdiagnostic risk factor for various mental and physical health conditions throughout life. However, less is known about the processes through which ACE are linked to multiple negative outcomes. A better understanding of the underlying processes is crucial for an improved insight into risk and resilience processes and for tailoring interventions.

The main aims of the FACE epidemiological study are to investigate the associations between ACE and psychological functioning and to investigate to which degree these associations are mediated by deficits in emotion regulation, social information processing and lower social support. It is the first study that links two strands of theory and research, i.e., emotion regulation and social information processing in the context of ACE, and analyses the short- and long-term longitudinal interplay of ACE, emotion regulation, social information processing, social support and psychosocial functioning. The results will substantiate the Integrative Model of Emotion Regulation and Social Information Processing in the Aftermath of ACE. The longitudinal design with a large sample size will provide an opportunity to provide new insights into causal mechanisms linking ACE to psychosocial functioning and to test moderating effects of several other factors such as gender or socioeconomic factors. With its large sample size, the study will allow to identify different patterns of ACE, providing new insights into how ACE co-occur and how these patterns are related to distinct trajectories of psychosocial functioning.

Furthermore, the FACE epidemiological study provides data on self-reported ACE as well as service use among young adults to inform healthcare policies and the provision of appropriate healthcare services. It prospectively identifies factors that facilitate or hinder service use in general and the use of the FACE self-help programme specifically. The FACE project examines which young adults are especially receptive to an intervention –and the age at which they would be most receptive—as well as seeking to identify the developmental stage (regarding life transitions) at which the intervention is most effective. The combined data of both subprojects provide the empirical basis to advance theory-driven models of enrolment and engagement with m-health interventions.

This study has several limitations. All data from participants are self-reported and thus subject to several types of bias, notably recall bias (especially events in early childhood), social desirability bias, non-response bias, or hesitation to answer sensitive questions. Data collection for the baseline assessment will take place during the ongoing COVID-19 pandemic, and the COVID-19 situation continues to have an impact on participants economic, social, and psychological situation, and may impact trends in psychosocial functioning. We will closely follow the further development of the pandemic and adjust for its effect where appropriate. Selective attrition between study wave is a potential limitation, as those with a more negative development of psychosocial functioning may reply less often to follow up. However, multiple imputation procedures can account for this.

In conclusion, the FACE project is the first study that links two strands of research and analyses the longitudinal interplay of emotion regulation and social information processing in young adults with and without ACE as: (a) long-term associations in a large sample of the epidemiological study; as (b) ecological momentary assessments; and (c) as targets of the m-health intervention. It takes patterns and dimensions of ACE as moderators into account and includes a comprehensive assessment of psychosocial outcome measures as dimensions and patterns of vulnerability and resilience. It will allow to investigate causal mechanisms linking ACE to psychosocial functioning, with a focus on social information processing, emotion regulation, and social and professional support.

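### Multiple imputation is triggered by a finding of missingness at random that observed data cannot supply, and is said without condition to deal with dropout among those who worsen

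*Protocol article*

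**What the plan says.** Under Statistical analysis, the paragraph on missing data promises missingness analyses that will "determine whether missing data are completely at random, at random or non-ignorable". The main method then depends on the answer: "If missingness at random is supported, we will use Multiple Imputations in Mplus". The sensitivity analyses will compare "different ways of imputing missing data including complete case analyses and if appropriate full information maximum likelihood". The same paragraph puts attrition at 40% by the fourth wave, leaving about 3000 of 5000.

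The limitations paragraph of the Discussion names the dropout the authors expect: "those with a more negative development of psychosocial functioning may reply less often to follow up". It closes the subject with "However, multiple imputation procedures can account for this". No condition is attached.

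The Abstract makes psychosocial functioning over the study period the primary outcome. Under Statistical analysis, growth mixture models are to find chronically dysfunctional, recovering and resistant groups.

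**The concern.** Two statements are wrong as written.

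First, MAR and MNAR differ only in whether dropout depends on values nobody recorded, given those that were. No analysis of the recorded data can decide between them, so the choice of main method hangs on a result that cannot be obtained.

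Second, the Discussion ties non-response to the course of the primary outcome itself. Waves are a year apart, so a participant can worsen after one questionnaire and skip the next without the decline being recorded. Standard imputation fills that gap as if the participant had gone on like responders with the same history.

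At stake are the results on change. If people who deteriorate leave, the average course looks better than it was, and imputation, complete-case and maximum likelihood results can all err in the same direction. Agreement among them would not test the mechanism the authors describe.

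**Working it through.** **Inputs from the article.** Baseline 5000; attrition 40% at wave 4; 25% reporting ACE (1250); four yearly waves; imputation conditional on MAR.

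**The plan's own figure.** 5000 × (1 − 0.40) = 3000. It reproduces.

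**Why the trigger fails.** Let dropouts' wave-4 mean, given everything recorded, lie δ below that of responders with the same record. MAR implies δ = 0. Every value of δ leaves the recorded data unchanged and so fits them equally well. The data can show which recorded variables predict dropout; they carry no information on δ.

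**Size at the stated attrition.** The MAR-imputed wave-4 mean is too high by 0.40 × δ. The δ values are assumptions.

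| δ (SD) | Error in wave-4 mean (SD) |
|---|---|
| 0.1 | 0.40 × 0.1 = 0.04 |
| 0.2 | 0.40 × 0.2 = 0.08 |
| 0.3 | 0.40 × 0.3 = 0.12 |
| 0.5 | 0.40 × 0.5 = 0.20 |

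**ACE contrast.** With 40% dropout in both groups, the error is 0.40 × (δ in ACE group − δ in others). Equal δ gives zero. If δ were 0.5 and 0.2, it would be 0.40 × 0.3 = 0.12 SD.

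**Illustrative simulation.** 5000 people, 25% ACE, four waves, 40% missing at wave 4 only, 60 replicates, 20 imputations from ACE, waves 1 to 3 and their interactions. Assumed, not in the article: outcome SD about 1; ACE effect −0.5 at wave 1 and −0.8 at wave 4; log-odds of dropout rising 0.25, 0.5 or 1.0 per SD of worsening. Expected mean change is 0.25 × (−0.3) = −0.075 SD.

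| Dropout depends on | Log-odds per SD | True change | Imputation | Complete case |
|---|---|---|---|---|
| decline recorded by wave 3 (MAR) | 0.25 | −0.075 | −0.074 | −0.017 |
| same | 0.5 | −0.075 | −0.074 | +0.034 |
| same | 1.0 | −0.077 | −0.078 | +0.116 |
| unrecorded decline, wave 3 to 4 (MNAR) | 0.25 | −0.078 | −0.011 | −0.024 |
| same | 0.5 | −0.074 | +0.054 | +0.023 |
| same | 1.0 | −0.075 | +0.157 | +0.098 |

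Under MAR, imputation recovers the truth. In the MNAR rows its error is 0.067, 0.128 and 0.232 SD. Dividing by 0.40 gives implied δ of about 0.17, 0.32 and 0.58 SD. Complete case errs the same way, by 0.054, 0.097 and 0.173. The two methods differ by only 0.013, 0.031 and 0.059, so comparing them would hide most of the error.

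In the MNAR rows the true wave-4 ACE contrast was −0.80 to −0.81 and imputation gave −0.79 to −0.81. Dropout was nearly equal in the two groups (about 41% against 40%).

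**The case against.** The strongest reply is that the Discussion says only that imputation can help, and often it will. Almost all measures are repeated at every wave, so much of a decline may be recorded before someone drops out, and the MAR rows above show imputation working well there. This stands. A reader might infer that imputation does nothing for selective attrition, or that the article describes an MNAR mechanism outright. Neither follows: the text does not say the decline goes unrecorded. The fault is the missing condition.

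A second reply is that this is a journal article, and the handling of non-ignorable missingness may be set out in a fuller plan. This also stands: the absence of an MNAR analysis, or of a branch for MAR not being supported, is not a finding in itself. The two statements that are in the article remain wrong.

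Third, a reader might infer that every planned sensitivity analysis assumes MAR or something stronger. The article does not settle this. Its list is open-ended and could take in an MNAR imputation, and complete-case regression can be valid when missingness depends only on covariates. What can be said is that no MNAR method is named.

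Finally, the dropout strengths are assumed and only mean change was simulated. No growth mixture model was fitted, so a distortion of trajectory classes is plausible but not computed.

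**Conclusion.** The point holds in a limited form. Choosing imputation on a determination that missingness is at random cannot be carried out, and the claim in the Discussion is true only under MAR given the variables in the imputation model. The sensitivity analyses named would not test dropout driven by decline in the year before a missed wave.

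The size that rests least on modelling is 0.04 SD in the wave-4 mean per 0.1 SD of δ at 40% attrition. The 0.1 to 0.5 SD range for δ is an assumption. The simulated reversals, where a true decline appears as improvement, show what is possible, not what is expected.

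The main exposure is in mean change and trajectories. A reader might infer that the association of ACE with functioning is biased too. The check does not support that unless outcome-dependent dropout differs by ACE. Severity: should-fix.

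**What to change.** - In the missing-data paragraph, replace the promise to determine the mechanism with one to describe who drops out and which recorded variables predict it.
- Use multiple imputation or full information maximum likelihood with auxiliary predictors of dropout unconditionally.
- In the Discussion, say that imputation accounts for selective attrition only under MAR given those variables.
- Pre-state one MNAR sensitivity analysis for psychosocial functioning: delta-adjusted imputation over a stated range, with δ allowed to differ by ACE, or a pattern-mixture or selection growth model in Mplus. With delta adjustment, report the δ at which conclusions change.

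The cost is revised wording and a few more model runs in the same software. No new data are needed.
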